### Sample size

The sample size of 270 participants is based on a power calculation. A review of earlier studies on the effects of cognitive rehabilitation in MS [14] suggests that we can expect moderate effects (effect size of 0.35) between pre- and post-intervention. Assuming statistical significance of 0.025, a power of 0.80, and an effect size of 0.35, 75 participants per group are needed. A conservative alpha of 0.025 has been chosen to take into account that we compare two interventions with a control group. A correlation of 0.6 between the measures was assumed. Based on previous experiences, a drop-out of 20% over the study period is expected. Therefore, we will include 90 subjects per group to ensure sufficient power. This study will be carried out using an intention-to-treat protocol. Therefore, subjects who withdraw from the study after inclusion will not be replaced.

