### Allocation and blinding

After baseline measurements, participants will be randomly assigned to one of the three conditions with a 1:1:1 allocation using a block randomisation of Research Randomizer (https://www.randomizer.org) to ensure equal group sizes. The block randomisation will not be disclosed to researchers performing measurements and analyses. After receiving informed consent, the involved lifestyle coach or work coach will be informed of the inclusion of the participant in their treatment arm by a researcher who is not involved with the measurements and analyses. Cognitive measures, structural and functional brain measures, neurological-, blood-, and physiological measures will be collected, analysed, and stored under a single-blinded protocol. To achieve single blinding, eligible participants will be randomised and assigned to an intervention by three designated researchers ([name]) who are not involved in data collection and analyses. The researchers who are involved in data collection and analyses ([name]) are not informed about the allocation, nor discuss the intervention with the participants and involved coaches. In addition, researchers who carry out the measurements will explicitly instruct participants not to disclose any information about the intervention they are following.

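### With the expected 20% drop-out, 90 per group leaves about 72 completers, slightly below the 75 that the protocol says it needs (minor)

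*Protocol article*

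**What the plan says.** All the figures are in the Sample size section of the protocol article. The total is presented as calculated: "The sample size of 270 participants is based on a power calculation". The requirement per group is explicit: "Assuming statistical significance of 0.025, a power of 0.80, and an effect size of 0.35, 75 participants per group are needed". The significance level is explained by the two comparisons with control: "A conservative alpha of 0.025 has been chosen to take into account that we compare two interventions with a control group". Whether it is one- or two-sided is not stated. On attrition, the section states the expected loss and draws the consequence from it: "Based on previous experiences, a drop-out of 20% over the study period is expected. Therefore, we will include 90 subjects per group", with adequate power as the stated purpose. The section then refers to intention-to-treat and adds that "subjects who withdraw from the study after inclusion will not be replaced".

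Under Allocation and blinding, participants are "randomly assigned to one of the three conditions with a 1:1:1 allocation", so 270 means 90 in each arm. No formula for the drop-out allowance is printed.

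**The concern.** The text presents 90 as the consequence of applying a 20% loss to a requirement of 75. If that were so, 80% of 90 should be at least 75, and it is not. Three printed numbers (75 needed, 20% lost, 90 enrolled) therefore disagree, and with replacement excluded, enrolment offers no other margin.

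What is at stake is the accuracy of the power statement. If drop-out runs as the trial team expects, each arm ends a little below its declared requirement. A results paper repeating that 270 gave 80% power with allowance for 20% drop-out would then be slightly wrong. The validity of the treatment comparison and the type I error rate are not affected.

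**Working it through.** **Inputs** (all from Sample size, except the allocation ratio): required number per group 75; drop-out 20%; enrolled per group 90; total 270 with 1:1:1 allocation; alpha 0.025; power 0.80; effect size 0.35; correlation 0.6.

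**1. Reproducing the plan's figure.** 75 × (1 + 0.20) = 90, and 3 × 90 = 270. The match is exact. Multiplication by 1.2 is nevertheless an inference, because the article does not show how 90 was obtained.

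**2. What remains after 20% loss.** 90 × (1 − 0.20) = 72 per group; 3 × 72 = 216. The stated requirement is 75 per group; 3 × 75 = 225. The shortfall is 3 per group, 9 in total. This step needs only the printed figures, however 90 was reached.

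**3. Number that would keep 75 after 20% loss.** 75/(1 − 0.20) = 93.75, rounded up to 94 per group; 3 × 94 = 282, which is 12 more than 270. Check: 94 × 0.80 = 75.2. Rounding does not explain 90.

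**4. Drop-out that 90 per group can absorb.** 1 − 75/90 = 16.7%.

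**5. Effect on power, completers only.** Assume that 75 per group gives exactly 80% power. Power then depends on the square root of the ratio of sample sizes:

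Power at 72 = Φ[(z for alpha + z for power) × √(72/75) − z for alpha], with √(72/75) = 0.9798.

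- Alpha 0.025 two-sided: Φ[(2.241 + 0.842) × 0.9798 − 2.241] = Φ(0.779) = 0.782.
- Alpha 0.025 one-sided: Φ[(1.960 + 0.842) × 0.9798 − 1.960] = Φ(0.785) = 0.784.

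Either way power is about 78%, a loss of roughly 2 percentage points.

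**6. Why the 78% must stay conditional.** Step 5 does not use the stated effect size or correlation; it takes 75 as correct. The article does not say which test the 75 refers to, and the stated inputs do not clearly lead to it. For example, a two-sided 0.025 comparison of two groups adjusted for baseline needs 2 × (1 − 0.6²) × (2.241 + 0.842)²/0.35² = 99.3, or 100 per group. On that reading, 72 per group gives Φ[(0.35/0.8) × √(72/2) − 2.241] = Φ(0.384) = 0.65. Where 75 comes from is a separate question. It does not change steps 1 to 4, but it means that 78% cannot be called the power under the stated assumptions without the condition.

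**The case against.** Three objections deserve a hearing.

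**The primary analysis is not restricted to completers.** Statistical analysis makes intention-to-treat the main focus, plans a mixed model over T0 to T3 with subject as random factor, and plans multiple imputation for missing follow-up on outcomes other than the digital questionnaires. A participant lost late still contributes earlier measurements. This stands, and it limits the consequence: the effective loss may be smaller than 72 against 75 suggests. It does not repair the sum, because the Sample size section does not rely on partial data; it offsets the loss by enrolment alone.

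**Timing.** The 20% applies to the whole study, which runs to month 16, while the effect size is for change from before to after the intervention, and the first measurement after it is at month 4. Drop-out by month 4 can be no higher than the 16-month figure and might be within 16.7%. This is possible, but the article gives no month-4 drop-out, does not name a single primary time point, and does not argue this way.

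**Drop-out expressed relative to those retained.** Fifteen lost against 75 kept is 20% of 75, but it is 15/90 = 16.7% of those enrolled. Drop-out over a study is naturally read as a share of those included, so this reading does not rescue the sentence.

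A reader might go further and infer that nothing can restore the shortfall, that the trial fails to deliver its power, or that 282 participants must be recruited. The documents do not support these readings. The planned analysis can recover some information, the loss on the plan's own terms is about 2 power points, and a corrected sentence resolves the inconsistency without more participants.

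**Conclusion.** The inconsistency is real and follows from the printed figures: 20% loss from 90 leaves 72 per group, 3 short of the stated 75, and no other section corrects this. Multiplication by 1.2 is the likely cause but is inferred. The size is small: an allowance that covers 16.7% instead of 20%, and power of about 78% instead of 80%. The power figure assumes that 75 gives exactly 80% at alpha 0.025 and that only completers count; the mixed model and imputation may narrow the gap. Severity: minor. It is a statement to correct, not a flaw in the design.

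**What to change.** Keep 270 and replace the drop-out sentence in Sample size with one that says three things:

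- with the expected 20% drop-out, about 72 of 90 participants per group complete, slightly below the 75 required;
- 75 per group are retained only if drop-out is at most 16.7%;
- with 72 completers, power is slightly below 80%: about 78%, if 75 per group gives 80%.

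Stating the 16.7% allowance alone would not be enough, because the team's own expectation of 20% would still exceed it. If the sponsor relies on partial data from participants who drop out, the sentence can say so.

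The cost is one or two sentences and a slightly less favourable power statement. Enrolment, design and analysis do not change, and the total of 270 given elsewhere in the article stays as it is.

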### Recruitment

Most of the participants participated in work package 1 before participating in the current study. These participants will mainly be recruited through 12 hospitals in the Netherlands, each having an MS population of 250–650 people. Of the 750 participants who take part in work package 1, we expect that approximately 30% has mild cognitive deficits [102], and therefore 220 participants who can enrol in the current study. The remaining 50 participants will be recruited through social media, and we can approach potential participants for this study by contacting PwMS who gave permission to be approached for further research projects. PwMS who are willing to participate will be checked for eligibility based on the in/exclusion criteria. People who are eligible to participate in work packages 2 and 3 will receive an information letter and will be asked to sign informed consent.

### Allocation and blinding

After baseline measurements, participants will be randomly assigned to one of the three conditions with a 1:1:1 allocation using a block randomisation of Research Randomizer (https://www.randomizer.org) to ensure equal group sizes. The block randomisation will not be disclosed to researchers performing measurements and analyses. After receiving informed consent, the involved lifestyle coach or work coach will be informed of the inclusion of the participant in their treatment arm by a researcher who is not involved with the measurements and analyses. Cognitive measures, structural and functional brain measures, neurological-, blood-, and physiological measures will be collected, analysed, and stored under a single-blinded protocol. To achieve single blinding, eligible participants will be randomised and assigned to an intervention by three designated researchers ([name]) who are not involved in data collection and analyses. The researchers who are involved in data collection and analyses ([name]) are not informed about the allocation, nor discuss the intervention with the participants and involved coaches. In addition, researchers who carry out the measurements will explicitly instruct participants not to disclose any information about the intervention they are following.

### Data capture and data monitoring

Before the start of recruitment, study researchers responsible for data collection are trained on the use of assessments. All study data, except the structural and functional MRI data, are stored in Castor Electronic Data Capture (EDC) system, which is a secure, web-based application with features like audit-trails, monitoring, and capturing and integrating external data. Additionally, regular monitoring will be carried out through the sponsor to ensure data quality, accuracy, and GCP adherence. Collected data will be stored using a code and will always be checked by a second researcher to minimise input errors. Imaging data will be stored on the image data server of the hospital.

### Statistical analysis

Data will be analysed using R (R Core Team, Vienna, Austria) and Rstudio version 4.2 or higher (PBC, Boston, MA) and/or SPSS version 28 or higher (IBM, Armonk, NY). Analyses will be performed according to intention-to-treat and per-protocol. The main focus of the analyses will be on the intention-to-treat analysis, as this will reduce bias and better represents daily practice. A per-protocol analysis will be performed to evaluate the effect of the intervention on itself, supplementary to the intention-to-treat analysis. Data will be included in the per-protocol analysis if the participant completed the intervention. The alpha level will be set at a statistical threshold of α = 0.05, corrected for multiple comparisons when applicable. GAS will be used to discriminate between responders and non-responders concerning the interventions.

For the outcome cognitive functioning we will calculate a reliable change index (RCI) for each cognitive test based on the enhanced usual care group. Using the RCI scores allows us to correct for learning effects. An RCI score above + 1.64 or below -1.64 is assumed to reflect significant improvement or decline, respectively [5, 103]. The psychological and work functioning data will be obtained via questionnaires and will be analysed as continuous variables together with the physiological data. MRI images will be analysed using FSL (https://fsl.fmrib.ox.ac.uk) and Freesurfer (Charlestown, Massachusetts). Data obtained (atrophy, white matter integrity, task-specific brain activation and brain connectivity) will be exported to Rstudio after which mixed-model analyses will be performed.

Missing data will be minimised by using digital questionnaires, that prompt participants to answer each question before being allowed to proceed. For other outcome measures, multiple imputation will be used for missing baseline and follow-up data. Outliers will be identified and excluded from the main analysis.

Primary analyses will evaluate the effectiveness of the investigated interventions (‘strengthening the brain’, ‘strengthening the mind’) compared to a control group (‘enhanced usual care’) in improving HRQoL (overall score on SF-36). A mixed-model analysis will be performed, with time (T0, T1, T2, and T3) and condition (‘strengthening the brain’, ‘strengthening the mind’, and ‘enhanced usual care’) as fixed factors, and subject as random factor. P-values and estimates of effect sizes will be obtained. Additionally, separate mixed-model analyses will be performed to evaluate the effect of the investigated interventions compared to the control group on cognitive, psychological, physiological, and work functioning, and enhancing the brain’s functional network. Predictors of treatment response will be investigated by adding baseline scores on the biological, psychological, and environmental measures to the mixed-model analyses.

Mediation analyses will be used to study which mechanisms (i.e.., biological, psychological, and environmental) mediate the effect of the interventions on HRQoL. Conditions for mediation will be tested [104]: 1) investigated interventions should affect HRQoL; 2) investigated interventions should affect the presumed mediator; 3) presumed mediator and HRQoL should be related.

The cost-effectiveness analyses will be performed from a healthcare and a societal perspective according to the intention-to-treat principle. Intervention costs will be calculated using a bottom-up micro-costing approach. Missing cost and effect data will be imputed using multiple imputation by chained equations (MICE) with predictive mean matching to account for the skewed distribution of costs. The number of imputed datasets will be increased until the loss of efficiency is smaller than 5% [105]. Each dataset will be analysed separately as described below, after which results will be pooled using Rubin’s rules. Bivariate regression models will be used to estimate cost and effect differences between the intervention groups and the control group, while adjusting for confounders if necessary. Incremental cost-effectiveness ratios will be calculated by dividing the difference in costs by the difference in effects. Statistical uncertainty will be estimated using bias-corrected and accelerated bootstrapping and will be presented in cost-effectiveness planes and acceptability curves. Sensitivity analyses are performed to assess the robustness of the results.

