**Methods:**

Randomised controlled trial including 270 PwMS with mild cognitive impairment, who have paid employment ≥ 12 h per week and are able to participate in physical exercise (Expanded Disability Status Scale < 6.0). Participants are randomised across three study arms: 1) ‘strengthening the brain’ – a lifestyle intervention combining personal fitness, mental coaching, dietary advice, and cognitive training; 2) ‘strengthening the mind’ – a work-focused intervention combining the capability approach and the participatory approach in one-on-one coaching by trained work coaches who have MS themselves; 3) Control group—receiving general information about cognitive impairment in MS and receiving care as usual. Intervention duration is four months, with short-term and long-term follow-up measurements at 10 and 16 months, respectively. The primary outcome measure of the Don’t be late! intervention study will be HRQoL as measured with the 36-item Short Form. Secondary outcomes include cognition, work related outcomes, physical functioning, structural and functional brain changes, psychological functioning, and societal costs. Semi-structured interviews and focus groups with stakeholders will be organised to qualitatively reflect on the process and outcome of the interventions.

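### The control-normed change index for cognition does not isolate learning, its place in the mixed model is not stated, and a baseline-adjusted continuous score would be more efficient

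*Protocol article*

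**What the plan says.** The Statistical analysis section of the protocol article treats cognition separately from the other outcomes. It says "we will calculate a reliable change index (RCI) for each cognitive test based on the enhanced usual care group", gives as the reason "Using the RCI scores allows us to correct for learning effects", and adds a reading rule: "An RCI score above + 1.64 or below -1.64 is assumed to reflect significant improvement or decline, respectively". No formula for the index is given. The next sentence says that the psychological and work questionnaire data "will be analysed as continuous variables together with the physiological data"; nothing comparable is said of cognition.

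Later in the same section the between-arm analysis is described: "separate mixed-model analyses will be performed to evaluate the effect of the investigated interventions compared to the control group on cognitive" and other functioning. Whether the raw test score, the continuous RCI or the RCI category is the dependent variable is not stated. The only mixed model set out in detail, the one for the SF-36, has T0, T1, T2 and T3 as levels of time.

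Cognition is secondary. The abstract says: "Secondary outcomes include cognition, work related outcomes, physical functioning".

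**The concern.** Three things do not fit together.

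- **The rationale.** Mean change in the control arm is not a pure learning effect. Over 4, 10 and 16 months it also contains disease change. It contains regression to the mean as well, because entry requires at least one low test score (Study population) and overlapping results from work package 1 are carried into this trial (Study design and setting). Practice effects shared by the arms are already removed by comparing randomised groups.
- **The model.** An RCI describes change from baseline, so it has no meaningful value at T0. The one model that is spelled out includes T0 as an outcome time.
- **Efficiency.** If the RCI is a standardised simple change score, it uses the baseline less well than covariate adjustment does. If its category were used, much more would be lost.

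At stake are the precision and the reading of the cognitive results. The trial aims to postpone cognitive decline, and a score centred on the controls cannot show how much the controls declined.

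**Working it through.** The article gives no power figure for cognition, so there is none to reproduce. The inputs below are borrowed from its Sample size section, and applying them to a cognitive test is an assumption.

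**Inputs**
- Effect 0.35, taken in units of the raw-score SD; correlation between measures ρ = 0.6.
- 90 per arm, 20% drop-out: 90 × 0.8 = 72 per arm analysed.
- Two-sided alpha 0.05, the general level in Statistical analysis, before any correction.
- RCI cut-off 1.64.
- Normal scores and equal SDs in both arms.

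The article's 75 per group at 80% power is a separate matter and is not relied on here.

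**1. Control-arm labels**

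With the control arm's own mean and SD of change as the norm, control RCIs have mean 0 and SD 1. The share beyond each cut is 1 − Φ(1.64) = 0.0505. About 5% are improved and 5% declined on each test, whatever the controls' true course.

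**2. Power for one intervention against control**

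Power ≈ Φ(δ/SD × √(n/2) − 1.96), with √(72/2) = 6.

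- *Continuous change-type RCI.* SD of change = √(2(1 − 0.6)) = 0.894. Standardised effect 0.35/0.894 = 0.391. Power = Φ(0.391 × 6 − 1.96) = Φ(0.39) ≈ 65%. Rescaling by a constant changes nothing: simulated p-values for the RCI and for raw change were identical to rounding error.
- *Baseline-adjusted score.* Residual SD = √(1 − 0.6²) = 0.80. Standardised effect 0.35/0.80 = 0.4375. Power = Φ(0.4375 × 6 − 1.96) = Φ(0.665) ≈ 75%.
- *Improved, yes or no, at +1.64.* Treated share = 1 − Φ(1.64 − 0.391) = 10.6%, against 5.05% in controls. A two-proportion z test has power of 23% by the normal approximation and 24% by exact enumeration.

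| Form of the cognitive outcome | Alpha 0.05 | Alpha 0.025 |
|---|---|---|
| Continuous score, baseline as covariate | 75% | 65% |
| Continuous change-type RCI | 65% | 54% |
| RCI category above +1.64 | 23-24% | 15-16% |

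The variance ratio of adjusted score to change score is 0.64/0.80 = 0.8. The adjusted analysis therefore needs about 20% fewer participants for the same power.

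**3. Does norming on the control arm bias the comparison?**

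In 3,000 simulated trials per setting (75 per arm, ρ = 0.6, alpha 0.025), the control arm drifted by −0.3, 0 or +0.3 SD. The between-arm difference stayed at 0.35. For the continuous score, type I error was 2.2-2.5% and power 55-56%. The same constant is subtracted in every arm and cancels.

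**The case against.** The strongest reply is that the text does not make the RCI category an endpoint. Cognition is listed for the same mixed-model approach as outcomes that are called continuous. The MRI measures are not called continuous either, yet they go into mixed models. The ±1.64 sentence only interprets an individual's score, and the exact model variable may be set in an analysis plan that is not at hand. This stands. A reader might infer from the contrast with the continuous outcomes that cognition is tested by category and that most of the power is thrown away; the document does not support that as a statement of fact.

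Further inferences are also unsupported:

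- *That subtracting control-arm change biases the treatment effect.* It does not, as step 3 of the working shows.
- *That a stable participant would readily be called improved.* On these inputs, a participant with no observed change crosses +1.64 only if controls fall on average by 1.64 × 0.894 = 1.47 SD. Nothing in the article suggests such a fall.
- *That many participants would be flagged by chance across the battery.* The index is defined per test, and no rule of the kind 'at least one test' appears.
- *That the RCI breaks the analysts' blinding.* Any comparison of an intervention with control requires the control arm to be identified, so this is not particular to the RCI.

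It is also fair to say that no RCI formula is given. If the index already adjusts for baseline, the gap between 65% and 75% shrinks or disappears.

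What the reply leaves untouched is the stated rationale, the loss of information about the controls' own course, and the mismatch between a change index and a model with T0 as a level.

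**Conclusion.** The point holds as a minor to moderate one on a secondary outcome; the primary SF-36 analysis is not affected. The article describes as a correction for learning what is really change relative to enhanced usual care, and it does not say which form of the cognitive score is modelled. The between-arm contrast remains valid.

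The likely cost is efficiency: about 10 percentage points of power (65% against 75%) if the RCI is a continuous change-type score. The fall to about 23-24% is conditional on the category being the endpoint. These figures assume an effect of 0.35 raw SD, a correlation of 0.6, 72 per arm, normal scores with equal SDs, a single post-baseline comparison, and an RCI without baseline adjustment. A higher baseline correlation would narrow the gap between the two continuous analyses, and a lower one would widen it.

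**What to change.** State the cognitive analysis explicitly, for example: *each cognitive test is analysed as a continuous score at T1, T2 and T3 in a mixed model, with that test's baseline score as covariate, and each intervention is compared with enhanced usual care at each time point.*

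Keep the ±1.64 RCI categories as descriptive only, give their formula, and describe them as change relative to enhanced usual care, not as a correction for learning. Show mean scores over time by arm next to them, so that any decline in the control arm is visible.

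The baseline scores are already collected and the software is the same, so the cost is wording. The downside is that effects are then reported in score units and the percentages of individuals who improve or decline move to a descriptive table.

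### Excluding outliers from the main analysis conflicts with the declared intention-to-treat analysis and can pull the treatment effect towards zero

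*Protocol article*

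**What the plan says.** In the protocol article, Sample size commits the trial to intention-to-treat: "This study will be carried out using an intention-to-treat protocol". Statistical analysis repeats this and gives the reason: "The main focus of the analyses will be on the intention-to-treat analysis, as this will reduce bias and better represents daily practice". The paragraph on missing data in that section then ends: "Outliers will be identified and excluded from the main analysis". No outcome, time point, threshold or unit (single value or whole participant) is attached to the sentence, and it is not restricted to erroneous or impossible values.

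Allocation and blinding places randomisation after the baseline measurements: "participants will be randomly assigned to one of the three conditions with a 1:1:1 allocation". The primary outcome is the SF-36 overall score, analysed over all four time points: "A mixed-model analysis will be performed, with time (T0, T1, T2, and T3) and condition". The only sensitivity analyses mentioned are in the cost-effectiveness paragraph. For the primary outcome, no analysis that keeps the outliers is stated.

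**The concern.** An intention-to-treat analysis keeps every randomised participant and their observed outcomes, so that the arms differ only by allocation and chance. A rule that removes values because they are extreme selects on the outcome after allocation. If an intervention changes how often extreme values occur, the rule removes different proportions from each arm, and the values it removes carry part of the effect.

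That matters in this trial. The interventions aim to prevent cognitive decline and job loss, and a large fall in quality of life is a plausible consequence of either. Elsewhere in Statistical analysis, large individual changes are treated as signal: a reliable change index beyond ±1.64 on a cognitive test counts as real improvement or decline. Input errors already have their own control, since Data capture and data monitoring provides for a check by a second researcher. The outlier sentence therefore reaches, as written, beyond error cleaning to genuine responses. At stake are the primary estimate and the power to detect it.

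**Working it through.** **1. The passages side by side.** Intention-to-treat is the main analysis (Sample size; Statistical analysis). Outliers leave the main analysis (Statistical analysis). Randomisation comes after T0, so T1 to T3 are all post-randomisation. The two statements conflict whatever threshold is later chosen: a definition fixes which values go, not whether their removal fits intention-to-treat.

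**2. Inputs for the size.** The plan gives no figure for the outlier rule, so there is none to reproduce. From Sample size: effect size 0.35, correlation 0.6, alpha 0.025, 75 per group. Assumed, because the article is silent: the cut-offs (2, 2.5 or 3 SD, or 1.5 × IQR), applied to all arms together, and the pattern of the effect. Model: follow-up score = 0.6 × baseline + √(1 − 0.6²) × noise = 0.6 × baseline + 0.8 × noise, plus the effect; one intervention arm against control, one follow-up score.

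**3. Mean effect fixed at 0.35 SD** (75 per arm, ANCOVA, two-sided 0.025, 4,000 runs). Rules were applied to the follow-up score or to the change score; ranges cover both. A responder's gain is the mean effect divided by the responder share: 0.35/0.25 = 1.4 SD and 0.35/0.15 = 2.33 SD. Change in the estimate after exclusion:

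| Effect pattern | 3 SD | 1.5 × IQR | 2 SD |
|---|---|---|---|
| Uniform shift | −1% | −4% | −15% to −17% |
| Carried by 25% responders | −3% to −4% | −9% to −11% | −26% to −29% |
| Carried by 15% responders | −13% to −15% | −30% to −41% | −49% to −58% |

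With all values kept, the estimate is about 0.35 in every row. Under the uniform shift, power falls from about 0.66 to about 0.65 (3 SD), 0.63 (IQR) and 0.55–0.56 (2 SD). With 15% responders it falls from about 0.45 to 0.35–0.36, 0.20–0.26 and 0.12–0.17, and the rules remove 1.2–8.7% of intervention values against 0–2.0% of control values. (That full-data power is below the planned 0.80 is a separate matter about the sample size and is not used here.)

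**4. Whole effect in preventing falls.** Assume 10% of controls and 3% of intervention participants have a 3-SD fall. True difference = 3 × (0.10 − 0.03) = 0.21 SD. In very large simulated arms:
- 3 SD rule: 0.16; loss (0.21 − 0.16)/0.21 = 24%.
- 2.5 SD rule: 0.11; loss (0.21 − 0.11)/0.21 = 48%.
- 1.5 × IQR rule: 0.085; loss (0.21 − 0.085)/0.21 = 60%. It excludes about 5.2% of controls and 1.8% of intervention participants.

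**5. Error rates and precision.** With no true effect, type I error stayed at 0.023–0.027 against the nominal 0.025, and nominal 97.5% intervals covered 0.971–0.976 of the time. Model standard errors tracked the empirical spread of the estimates under every pooled rule. In the scenario of step 4 with 75 per arm, nominal 95% intervals covered the true effect 83% (2 SD), 86% (IQR), 91% (2.5 SD) and 94% (3 SD) of the time, against 95% with all data. That shortfall comes mainly from the shifted estimate.

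**The case against.** **The size is assumed.** This stands. Step 4 puts the whole benefit in the tail, and nothing in the article says the effect has that shape. A reader might take 60% as the expected loss; the documents do not support that, and with a uniform shift and a 3 SD rule the loss is about 1%. The SF-36 is also bounded, while the simulations are not. With an assumed floor at −2.5 SD, the scenario of step 4 gave 0.165 without exclusion, 0.162 under 3 SD (2% lost) and 0.153 under IQR (7% lost). With a floor at −3 SD it gave 0.181, 0.182 and 0.133 (27% lost under IQR). The article gives no SF-36 SD that would place the floor.

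**Trimming makes the intervals too narrow.** A reader might infer this because trimming normal data at 2, 2.5 or 3 SD shrinks the SD by 12%, 4.5% or 1.3%. It does not follow: under a pooled rule the trimmed estimates also vary less, and step 5 shows matching standard errors and an unchanged type I error.

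**Analysts could choose whom to drop.** Allocation and blinding says those who collect and analyse data "are not informed about the allocation, nor discuss the intervention with the participants and involved coaches". This greatly limits arm-selective exclusion. It does not stop a blind pooled rule from trimming arms unequally when treatment changes the tails, as steps 3 and 4 show.

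**The definition may be in the full protocol or the SAP, and artefacts are plausible in MRI or physical tests.** Fair, so the missing definition is not the point made here. The unrestricted exclusion from the main analysis is stated, and a threshold set elsewhere would not reconcile it with intention-to-treat.

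**Conclusion.** The point holds. The article declares intention-to-treat as its main analysis and then removes outliers from that analysis without limiting this to errors. For T1 to T3 this is an outcome-dependent exclusion after randomisation.

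The consequence is possible attenuation, not a demonstrated large bias. It runs from about 1% (3 SD rule) to about 16% (2 SD rule) of a uniform 0.35 SD shift, and from about 25% (3 SD) to 60% (1.5 × IQR) if the whole effect is prevention of 3-SD falls on an unbounded scale; a floor on the scale could reduce the latter range sharply. These figures assume a pooled rule applied blind, removal of single values, and one follow-up score in place of the four-time-point mixed model. The conflict with intention-to-treat depends on none of them. The documents do not support a claim of inflated false positives or of materially understated standard errors.

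**What to change.** Replace the outlier sentence in Statistical analysis with:

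> *All verified observed values of all randomised participants are kept in the main analysis. Only values shown to be recording or measurement errors are corrected or set to missing, by staff blind to allocation. An analysis excluding or down-weighting extreme values is a sensitivity analysis.*

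The cost is this change of wording, one extra sensitivity analysis, and a slightly larger residual variance in the main analysis. The sample size does not change, and the edit can be made before unblinding.
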